### Sample size

A pilot study (unpublished) was carried out on preliminary data from 41 women with PCOS randomized to the pulse-based or TLC diet. Thirteen of the 41 women dropped out of the study giving a dropout rate of 32%. Changes in fasting glucose following the intervention (*n* = 28) was used to determine the required sample size for recruitment into the study. Changes in the mean fasting glucose were -0.18 and 0.14 mmol/L for the pulse-diet group and TLC group, respectively, with a population standard deviation of 0.46 and an effect size of -0.70. The pilot data provided 80% power for detecting a significant difference in fasting glucose concentration between groups (*p* < 0.05) following the intervention. It was determined 34 participants per group would be required for the study. Due to the dropout rate of 32%, the recruitment of 100 participants (i.e. 50 per group) was determined necessary.

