### Data management and analysis

The present study will follow intent to treat analysis with measurements and analysis carried out on all participants. All identifying information will be maintained on a secure University of Saskatchewan password protected drive that is shared only with principal investigators and primary research assistants identified on our ethics submission. All hard copies of identifiable information will be securely stored in a locked filing cabinet in a locked room with restricted access. A participant coding system will be used for all data collection which will be stored separately from identifying information.

All raw data obtained will be compiled and reviewed for accuracy on an Excel Spreadsheet. Descriptive statistics will be performed for all outcome measurements for the presentation of group data as means + standard deviation as well as to identify outliers and determine normality of the data.

The treatment effect on the dependent variables will also be assessed by a group by time ANOVA (baseline, 9- and 16-weeks), with repeated measures on the time factor using Statistica (Statsoft, Chicago IL). Any missing data points at 16-weeks will be accounted for by carrying forward the 9-week value. To verify this approach, we will also run a sensitivity analysis including only participants who complete all 3 time points. Any differences determined between the groups at baseline will be used as co-variates in our analysis. Questionnaire data (Quality of Life, Pulse Consumption, Physical Activity) will be presented descriptively. The participants and group categorization will be coded such that the investigators collecting and analyzing data are blinded to which diet the participants were following.

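### Carrying the week-9 value forward makes the 16-week comparison a mixture of two time points; it cannot work for follicle number, and agreement with completers does not verify it.

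*Protocol article*

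**What the plan says.** All of the analysis statements are in the protocol article under Data management and analysis.

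- Population: "The present study will follow intent to treat analysis with measurements and analysis carried out on all participants".
- Model: a "group by time ANOVA (baseline, 9- and 16-weeks), with repeated measures on the time factor".
- Missing week-16 values: "Any missing data points at 16-weeks will be accounted for by carrying forward the 9-week value".
- Check on that rule: "To verify this approach, we will also run a sensitivity analysis including only participants who complete all 3 time points".

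Under Sample size, on the pilot: "Thirteen of the 41 women dropped out of the study giving a dropout rate of 32" per cent. The recruitment target of 100 is built on that rate. Neither the timing of the drop-out nor its split by arm is given.

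The Design overview and Intervention sections schedule blood measures at week 9 and a repeat of the baseline assessments, which include the transvaginal ultrasound, at week 16. The Intervention section also says the length of treatment is required to observe changes in fertility-related outcomes. The Design overview names sex hormones, menstrual cycle length and follicle numbers as primary.

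**The concern.** Carry-forward is a fixed commitment in this document, not a detail left open. It treats a woman who misses week 16 as if her week-9 value were her week-16 value. The protocol offers no argument for a plateau at week 9, and for fertility-related outcomes its reason for the 16-week length points the other way.

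Three things follow.

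1. The 16-week group difference becomes a weighted mixture of the week-16 and week-9 differences. If drop-out differs between arms, any change common to both arms after week 9 also leaks into the comparison.
2. The rule needs a week-9 value. Women lost before week 9 have none, and follicle number has none for anyone, so the rule does not deliver the promised analysis of every participant.
3. The only check offered, a "sensitivity analysis including only participants who complete all 3 time points", removes the women whose handling is in question. It needs its own assumption about why they left.

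**Working it through.** **Inputs from the Sample size section.** Mean changes in fasting glucose of −0.18 (pulse) and 0.14 mmol/L (TLC); an SD stated as 0.46; a standardised effect stated as −0.70; 32% drop-out; 34 evaluable and 50 recruited per group.

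**The plan's own figures.** Difference: 0.14 − (−0.18) = 0.32 mmol/L. Standardised: 0.32/0.46 = 0.70. Drop-out: 13/41 = 31.7%. With a two-sided 5% t-test (sidedness is not stated), 34 per group gives 80.7% power. Recruitment: 34/(1 − 0.32) = 50 per group. All reproduce.

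**Assumptions needed.** The week-9 effect, the timing of drop-out, its split by arm, and a correlation of 0.5 between week-9 and week-16 changes (simulations only) are not in the document. Two timings are used: all drop-out after week 9 (the upper bound), and half before and half after, with early leavers having no value and being left out. Differences below are given as sizes.

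**Formula.** Let *c* be the share of analysed women whose value is carried forward. Expected 16-week difference = (1 − *c*) × week-16 difference + *c* × week-9 difference.

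**Shrinkage.** True difference 0.32, growing linearly, so the week-9 difference is 0.32 × 9/16 = 0.18.
- All after week 9, *c* = 0.32: 0.68 × 0.32 + 0.32 × 0.18 = 0.275, a loss of 14%.
- Half after week 9, *c* = 0.16/0.84 = 0.19: 0.81 × 0.32 + 0.19 × 0.18 = 0.293, a loss of about 8%.
- Other week-9 effects with *c* = 0.32: 0.22 if none is present by then, 0.32 if all is, 0.37 if it is 1.5 times as large.

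**Bias under no effect.** Both arms change by 0.2 after week 9; drop-out 42% v 22% (assumed). Bias = 0.2 × (difference in *c* between arms).
- All after week 9: 0.2 × (0.42 − 0.22) = 0.04.
- Half after week 9: *c* = 0.21/0.79 = 0.266 and 0.11/0.89 = 0.124, so 0.2 × 0.142 = 0.028.
- Simulation (50 per arm, SD of change 0.46, t-test on the 16-week change): type I error about 7% and 6% respectively, against 5%.

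**The completers check when drop-out is unrelated to outcome.** In the same simulations the completers' estimate is 0.32 in the shrinkage case and 0.00 in the no-effect case, with about 5% rejection in the latter. Here the check gives the right answer.

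**The completers check when drop-out depends on outcome.** A deliberately severe case: no true effect, 32% missing in each arm, the chance of missing week 16 rising with the unseen week-16 value in one arm and falling with it in the other. Completers give −0.34 with 94% rejection; carry-forward gives −0.12 with about 27%. Both err in the same direction, so agreement would mislead.

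**Availability of a value to carry.** Only blood is scheduled at week 9. Sex hormones and glucose therefore have a value to carry; follicle number, obtained by ultrasound, does not.

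**The case against.** The case for leaving the plan alone, or for treating this as minor, has real substance.

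- **The completers check is not worthless.** It is unbiased in both cases above where drop-out is unrelated to outcome, and a disagreement there would expose carry-forward. A reader might infer that agreement between the two analyses shows nothing at all. That goes too far: it is reassuring if drop-out is unrelated to outcome. It is insufficient on its own because that condition is untested.
- **32% is total drop-out.** Women who leave before week 9 cannot be carried forward, so the true share is smaller and the biases shrink, as shown.
- **Shrinkage does not always cost power.** In the linear-growth case with all drop-out after week 9, carry-forward rejects in about 84% of simulated trials against about 80% in completers. It distorts the estimate without hiding the effect.
- **A reader might infer that the rule inflates the planned test's false-positive rate to 20%.** That figure arises if a 0.32 difference at week 9 has vanished by week 16, tested by a 16-week t-test with all drop-out late (about 9% if half is early). But the planned test is a three-time-point group-by-time ANOVA, and a difference that comes and goes is a genuine interaction; it would usually reject even with complete data. The 20% is not an error rate of the planned test.
- **A reader might infer that women who miss only week 9 will be deleted, or that drop-out will be higher on pulses.** The article states no deletion rule. Nor does it give drop-out by arm; supplied meals could help or hinder retention.
- **The 16-week rationale is outcome-specific.** It concerns fertility-related measures. For glucose and insulin the duration rests on a review, and the magnitudes here are for fasting glucose, which belongs to the secondary metabolic set.

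What stands: the rule is stated, unjustified, can bias the 16-week comparison in either direction, and cannot operate for a primary outcome.

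**Conclusion.** The point holds in this bounded form. Carry-forward mixes week-9 and week-16 effects. On the fasting-glucose planning values the distortion is modest: 0.32 becomes 0.275 to 0.29 under linear growth, and under no effect with drop-out of 42% v 22% the bias is 0.03 to 0.04 with type I error of about 6% to 7% for a 16-week t-test. These sizes rest on assumed timing, split, correlation and week-9 effects; the direction cannot be known in advance. The primary outcomes have no planning values, so their bias cannot be sized.

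Two parts rest on no simulation. The rule supplies nothing for women lost before week 9 or for follicle number, so it does not itself achieve the analysis of all participants. And completers-only agreement cannot by itself verify it, because that analysis is biased whenever drop-out depends on outcome.

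**What to change.** - Delete the carry-forward rule.
- For outcomes measured at baseline, week 9 and week 16, fit a likelihood-based mixed model for repeated measures to all observed values, and name the 16-week group contrast as the test.
- For outcomes without a week-9 value, such as follicle number, use the observed baseline and week-16 values in the same kind of model, or multiple imputation.
- Keep the completers-only analysis as supplementary and stop describing it as verification.
- Add one sensitivity analysis that allows data to be missing not at random, such as delta-adjusted imputation. The mixed model still assumes that missingness is explained by the observed values.

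The cost is a change of analysis wording and slightly more programming. No new data, visits or participants are needed.

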### Randomization

During the 2-week lead-in period, participants will be randomized to either the pulse based diet or control TLC diet. Participants will be notified of diet allocation via email (and are not blinded). Randomization will be performed by an investigator who is not involved in obtaining or entering participant data. Randomization will be stratified based on the current use of the insulin sensitizing drug Metformin, using a computer-generated allocation schedule with a block size of 4.

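### Covariates are to be picked by observed baseline imbalance, so the adjusted model is not fixed in advance and forgoes the precision of prespecified baseline adjustment

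*Protocol article*

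**What the plan says.** Three statements in the protocol article bear on this point.

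- **Covariate rule** (Data management and analysis): "Any differences determined between the groups at baseline will be used as co-variates in our analysis". No list of candidate variables, test or threshold accompanies it.
- **Model** (same section): "The treatment effect on the dependent variables will also be assessed by a group by time ANOVA (baseline, 9- and 16-weeks". This is a repeated-measures model in which baseline is one of three responses, not a covariate.
- **Stratification** (Randomization): "Randomization will be stratified based on the current use of the insulin sensitizing drug Metformin", in blocks of 4. The analysis section does not mention Metformin.

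The Sample size section rests on a two-group comparison of change in fasting glucose: "Changes in the mean fasting glucose were -0.18 and 0.14 mmol/L for the pulse-diet group and TLC group, respectively". It pairs these means with an SD of 0.46, for a standardised difference of -0.70, and concludes: "It was determined 34 participants per group would be required for the study".

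**The concern.** Randomisation makes any baseline difference a matter of chance. A rule that turns such differences into covariates has three weaknesses.

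1. The final model is unknown until the baseline data have been examined, and with no stated criterion two analysts could reach different models.
2. Imbalance is the wrong selector. A covariate earns its place by predicting the outcome. A strongly prognostic variable that happens to be balanced is left out, and an irrelevant one that happens to be imbalanced is put in.
3. The rule fits poorly with the chosen ANOVA. If the outcome itself differs at baseline, the same value becomes both a response (the first time level) and a predictor.

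The rule also tends to keep out Metformin, the one factor the design singled out, because stratified blocks of 4 make it unlikely to be imbalanced.

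At stake are a treatment estimate whose model is settled after the data are seen, and precision that could be had at no cost.

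**Working it through.** **Inputs from the Sample size section.** Mean changes are -0.18 and 0.14 mmol/L, a difference of 0.32. The SD is 0.46, alpha 0.05 (sidedness not stated; two-sided reproduces the result), power 80%, 34 per group, dropout 32%.

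**Input not in the document.** The baseline-to-16-week correlation rho is assumed at 0.5 to 0.9, with equal variances at the two times.

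**Step 1: reproduce the plan's figure.** The standardised difference is 0.32/0.46 = 0.696. A two-sided two-sample t test at 5% needs 33.4 per group for 80% power, rounded up to 34. Allowing for dropout, 34/(1 - 0.32) = 50 per group, 100 in total. Power at exactly 34 per group is 81%. The plan's figure reproduces for an unadjusted comparison of change.

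**Step 2: effect of prespecified baseline adjustment.** With outcome variance s², a change score has variance 2s²(1 - rho), and a baseline-adjusted outcome has residual variance s²(1 - rho²). The ratio of adjusted to change is (1 - rho²)/[2(1 - rho)] = (1 + rho)/2. Holding the SD of change at 0.46, the standardised difference becomes 0.696/√((1 + rho)/2).

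| Assumed rho | Variance ratio | Standardised difference | Power at 34 per group |
|---|---|---|---|
| change score, as planned | 1.00 | 0.696 | 81% |
| 0.5 | 0.75 | 0.803 | 90% |
| 0.7 | 0.85 | 0.755 | 87% |
| 0.8 | 0.90 | 0.733 | 85% |
| 0.9 | 0.95 | 0.714 | 83% |

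**Step 3: does the stated rule recover that gain?** A simulation (6,000 replicates, 34 per group) added the outcome's baseline only when it differed between groups at p < 0.05. That threshold is an assumption.

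| rho | Quantity | Change score | Imbalance rule | Prespecified baseline |
|---|---|---|---|---|
| 0.5 | SD of estimate | 0.111 | 0.107 | 0.097 |
| 0.5 | Power | 81% | 82% | 90% |
| 0.7 | SD of estimate | 0.112 | 0.110 | 0.103 |
| 0.7 | Power | 81% | 81% | 86% |

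The rule recovers almost none of the gain. Its type I error was 4.0% (rho 0.5) and 4.2% (rho 0.7), so it was not inflated. The 86% here and the 87% in step 2 differ by simulation error.

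**Step 4: how often would the rule fire by chance?** If k independent variables were each tested at 5%, the chance of at least one difference is 1 - 0.95^k: 40% for k = 10 and 64% for k = 20. The article states neither a test nor a number of variables, and many of its measures are correlated. With 20 equally correlated variables the chance is 54%, 42% and 29% at pairwise correlations of 0.3, 0.5 and 0.7. These figures are illustrations only.

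**Step 5: the three-time group-by-time term.** For outcomes measured at all three times it has 2 numerator df and (68 - 2) × 2 = 132 denominator df. Under assumed compound symmetry, s²(1 - rho) = 0.46²/2 = 0.1058. The noncentrality is (34/2) × Σ(d_t - mean d)²/0.1058, where d_t is the group difference at each time.

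- Differences 0, 0.16, 0.32 (roughly linear growth): Σ = 0.0512, noncentrality 8.23, power 72%.
- Differences 0, 0.32, 0.32 (complete by week 9) or 0, 0, 0.32 (all after week 9): Σ = 0.0683, noncentrality 10.97, power 84%.
- Differences 0, 0.32, 0 (week 9 only): the same Σ, so also 84%, with no difference at 16 weeks.

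**The case against.** The strongest reply is that much of what one might infer from these passages goes further than the article allows.

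- **Baseline missing from the model.** A reader might infer this, and it is wrong: baseline is the first time level. What is true is that it is not a prespecified covariate.
- **Uncontrolled error rates.** A reader might infer this from the data-driven rule. The document does not support it, and the simulation found 4.0% to 4.2% when the rule was applied to the outcome's own baseline. Selection across many covariates was not tested. The article also blinds analysts to diet group, which limits any steering of covariate choice.
- **An underpowered trial.** On the change comparison, 34 per group gives 81%, as planned. The trial forgoes a gain, and that gain is small if rho is high.
- **Precision from stratification thrown away.** The Metformin point rests on silence in a condensed article. The planned test works on change, so a Metformin effect on outcome level but not on change cancels out. No figure is given from which a loss could be computed.
- **The 2-df test.** It applies only to bloods, which are taken at week 9. Follicle counts come from ultrasound at baseline and 16 weeks, so within the intervention their interaction has 1 df and is the change comparison itself. For bloods, the 72% to 84% range straddles 81%, so the direction depends on the trajectory.

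All of this narrows the point. None of it rescues the covariate sentence, which is a stated rule and not a detail left to an analysis plan.

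**Conclusion.** The point holds in narrowed form and should be acted on. The article fixes a covariate rule driven by chance imbalance, so the adjusted model is not set in advance and is not chosen for prognostic value. Compared with always adjusting for the outcome's baseline, the planned change comparison gives up 5% to 25% of its variance over assumed rho of 0.9 to 0.5. In power at 34 per group, that is 81% against 83% to 90%. This size rests on the assumed rho, on equal variances at the two times and on an SD of change of 0.46. Naming Metformin in the model is sound practice after stratifying on it, but its benefit cannot be quantified here. The 2-df test for bloods is a secondary matter: it answers a broader question than the one the sample size was built on.

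**What to change.** Delete the sentence on baseline differences and do not test baseline variables for significance. In its place, prespecify for every outcome two covariates, included whatever the observed balance: the outcome's own baseline value and the Metformin stratum. Take the adjusted group difference at 16 weeks as the test of the treatment effect, since the sample size rests on that comparison.

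For bloods, name the post-lead-in sample as the baseline, because bloods are drawn both before and after the lead-in. The text should also make clear that this sample precedes allocation: Design overview places randomisation after it, whereas the Randomization section places randomisation during the lead-in.

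The cost is analysis wording only. Both covariates are already collected, and the number recruited does not change.

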### Monitoring

Monitoring of the study will take place via yearly renewal of ethical approval. The ethics board has the option to review or inspect files at any time. Researchers will have regular contact with participants at the College of Kinesiology research gym facility where any adverse events can be reported. All adverse events will be recorded and University of Saskatchewan guidelines will be followed which require reporting of adverse events to the ethics board if the answer was yes to all 3 of the following: 1). Is the nature of the problem or event unexpected in terms of nature, severity or frequency?; 2). Is the nature of the problem or event related or possibly related (to the intervention)?; and, 3). Does the nature of the problem or event suggest that the research places participants or others at greater risk of harm (including physical, psychological, economic or social harm) than was previously known or recognized, or that were not described in the original application? Due to the short duration of the intervention and low likelihood that either diet will result in any adverse events of concern, there is no data monitoring committee, stopping guidelines or plans for interim analysis.

### Study status

This paper presents an ongoing study which includes follow-up measures that will be carried out. Following completion of the study, results will be presented in peer-reviewed scientific journals with focus on measures of infertility, metabolic syndrome, glucose response, diet, physical activity, and quality of life.

## Discussion

The present study is designed to determine whether a pulse-based diet is equally or more effective than a healthy control diet at reducing symptoms related to metabolic syndrome and reproductive dysfunction in women with PCOS. Although diet intervention studies in women with PCOS have been carried out, this is the first to determine the effects of a pulse-based diet in this population. The study design outlined has several features contributing to the novelty of this research. The diagnoses of PCOS used in dietary intervention studies have primarily used the Rotterdam criteria which defines polycystic ovaries as >12 follicles [42–44]. Recently, it has been suggested that the follicle count recommended by the Rotterdam criteria is too low due to improvements in resolving power of ultrasound images and an accurate diagnosis of PCOS requires a threshold of 26 follicles [21, 45]. The enhanced criterion used in the present study may allow for a more accurate representation of the PCOS population compared to similar intervention studies.

The present study takes a multi-disciplinary approach by incorporating measures from nutrition, physiology, kinesiology, psychology, and reproductive medicine. This approach allows for a comprehensive integration and association of the various components of PCOS which may lead to a better understanding of this multi-faceted syndrome. The inclusion of Kinesiology in the study produces unique data sets such as the use of accelerometers to quantify levels of activity which have been determined via self-reported questionnaires in previous reports [46, 47], 7-day activity records [48], physical activity recall [49] interviews [50], and Pedometer [51]. There is a paucity of physical activity data using accurate and objective measures in women with PCOS [52] and the present study utilizes information obtained using both physical activity questionnaires and accelerometers.

The baseline data collected as necessary for the analyses of the dietary intervention will also serve to characterize women with PCOS. The magnitude of our study with over 100 participants providing baseline measures, will result in an all-inclusive profile of women with PCOS which characterizes their lifestyle (i.e., diet including pulse consumption and exercise), quality of life, various health indicators for risk of disease (e.g., blood parameters, anthropometry, body composition) and infertility.

The primary significance of the research will be to further build on the resources used to develop evidence based dietary recommendations for women with PCOS. Lifestyle is currently the first line of action in treating many symptoms of PCOS and although some diets have been shown to improve specific symptoms of PCOS, there is currently no consensus on an optimal diet for women with the syndrome [53]. We expect to be able to demonstrate whether the insulin lowering effects of a pulse-based diet can better serve women with PCOS to reduce their symptoms.
